# Utilizing fNIRS to investigate the impact of Baduanjin training on attentional function in post-stroke cognitive impairment patients: a study protocol for a randomized controlled trial

**DOI:** 10.1186/s12906-023-04284-2

**Published:** 2024-01-11

**Keywords:** Baduanjin, Post-stroke cognitive impairment, Attentional lateralization, Randomized controlled trial

## Abstract

**Background:**

Post-stroke cognitive impairment (PSCI) is a prevalent complication among stroke survivors. It not only directly impacts patients' cognitive abilities but also hampers their capacity to regain independence in daily activities, consequently diminishing their quality of life. Among the various cognitive deficits following stroke, impaired attention is the most frequently observed, influencing not only daily functioning but also higher cognitive functions like working memory, executive functioning, and language.Emerging evidence indicates that Baduanjin, a traditional Chinese exercise, may have a positive impact on enhancing attention in older adults with mild cognitive impairment and stroke survivors. However, the precise mechanisms behind this effect remain unclear. In this study, we employed Baduanjin training as an intervention to address attention decline in post-stroke cognitive impairment patients and to delve into the potential mechanisms through which Baduanjin training may enhance attention in individuals with PSCI.

**Discussion:**

This trial aims to examine the impact of Baduanjin training on attentional lateralization among patients with post-stroke cognitive impairment (PSCI). Functional brain imaging utilizing near-infrared spectroscopy will be employed to investigate how Baduanjin exercise influences the structural and functional connectivity of distinct brain regions or brain networks.

**Trial registration:**

Chictr.org.cn, ID: ChiCTR2300076533. Registered on 11 October 2023.

## Introduction

### Background

Post-stroke cognitive impairment (PSCI) is a prevalent complication among stroke survivors, with approximately 50% of patients experiencing cognitive impairment in the early post-stroke phase [1]. Alarmingly, up to 32% of patients continue to suffer from cognitive impairment even three years after their initial stroke [2]. PSCI not only directly impacts patients' cognitive abilities [3] but also hinders their capacity to perceive and adapt to their external environment. It significantly disrupts the recovery of their daily living skills and diminishes their overall quality of life [4]. Moreover, the challenges in adhering to therapeutic instructions often have a profound impact on the efficacy and progress of rehabilitation training, further impeding functional recovery [5].

Impaired attention is one of the most common cognitive deficits following a stroke, with approximately 46% to 92% of patients experiencing attentional deficits in the acute phase [6]. These deficits persist in 20% to 50% of cases for several years post-injury [7, 8]. The attentional system comprises three functionally and structurally independent subsystems: vigilance, orienting, and executive control [9].Vigilance refers to the state of heightened sensitivity to external information and its maintenance. Orientation involves the selection of specific information from a vast amount of external input. On the other hand, executive control functions encompass the ability to execute complex behaviors, monitor, and resolve conflicts [10]. These three attentional subsystems are governed and processed by three distinct brain networks: the dorsal attention network (DAN), the ventral attention network (VAN), and the executive control network (ECN). These networks, while relatively independent, work in tandem to complete the attentional process and achieve cognitive control [11]. Our current study suggests that attention processing in the two hemispheres exhibits asymmetry, leading to a biased lateralization of the attentional network. Specifically, there is no significant lateralization for the vigilance function [12, 13]. However, significant left visual field-right hemisphere lateralization is observed for the subnetworks involved in orientation and executive control [14, 15]. Imaging studies have also revealed a strong right lateralization of the VAN in conjunction with the ECN, while the DAN exhibits a symmetrical distribution in both cerebral hemispheres. This implies that the attentional network displays a right-sided lateralization balanced with bilateral coordination, enhancing the efficiency of attentional processes while maintaining bilateral coordination.Nonetheless, it is this right-sided lateralization of attention that leads to the clinical prevalence and severity of left-sided attentional impairments resulting from right brain injuries [16]. Stroke patients experience attentional dysfunction due to damage to the dominant side of the brain region, disrupting the lateralization pattern of the attentional network. Previous studies have demonstrated that right hemispheric infarcts result in an advantage in left hemispheric orienting function processing, while left hemispheric infarcts lead to the loss of this advantage and impair orienting function [17]. Thus, the lateralization pattern of the attentional network in stroke patients is a crucial factor contributing to attentional dysfunction.

Baduanjin is a traditional Chinese health exercise, which is widely spread because of the advantages of soothing, simple, and high safety [18]. In recent years, Baduanjin exercises have found extensive application in stroke rehabilitation, demonstrating significant efficacy in primary stroke prevention, post-stroke motor function improvement, daily living activities, quality of life enhancement, balance function enhancement, and cognitive function improvement [19, 20]. A study involving 41 participants directly illustrated that six months of Baduanjin training led to improvements in overall cognitive function, executive function, and memory in patients with post-stroke cognitive impairment (PSCI). It also reduced alert reaction times and improved attention in these patients [21]. Other studies have indicated that Baduanjin, either alone or in conjunction with herbal or acupuncture therapies, can enhance attentional functions such as concentration in PSCI patients [22–24]. These findings suggest that Baduanjin has a positive impact on attention in individuals with PSCI, although the exact underlying mechanism remains to be elucidated.

Functional near-infrared spectroscopy (fNIRS) is a non-invasive brain imaging technique that relies on the varying absorption of near-infrared light within the 600–900 nm wavelength range by oxyhemoglobin and deoxyhemoglobin in brain tissue. This allows for real-time and direct detection of cortical oxygenation activity [25]. The relatively low cost of fNIRS, minimal requirements for testing environment and subject mobility, and few contraindications have led to a growing number of researchers utilizing fNIRS in stroke-related studies [26]. To investigate the effects and underlying mechanisms of 12 weeks of Baduanjin training on attentional lateralization and attentional networks in patients with post-stroke cognitive impairment (PSCI), we propose a prospective, randomized controlled trial (RCT). The primary goal of this trial is to assess the impact of octogenarian training on attentional lateralization in individuals with PSCI. Additionally, we seek to explore how Baduanjin exercise influences the structural and functional connectivity of specific brain regions and brain networks using near-infrared spectroscopic functional brain imaging.

## Methods

### Study design

The study design employed in this research is a randomized controlled trial, incorporating allocation concealment and assessor blinding. A total of 72 eligible participants will be randomly allocated to either the 12-week Baduanjin exercise intervention (with sessions lasting 40 min, conducted five times a week) or the 12-week regular activity control group.In addition to the Attentional Lateralization Index (ALI) and Overall Cognitive Functioning (OCF), which will be assessed by a professional evaluator using the Montreal Cognitive Assessment (MoCA) scale before the intervention and at the onset of the intervention (at weeks 6 and 12), cognitive dimensions will be evaluated using the Oxford Cognitive Screening (OCS-P) scale, motor function will be assessed using the Fugl-Meyer scale, participation level will be rated using the Pittsburgh Rehabilitation Participation Scale (PRPS), and activities of daily living will be measured. These assessments will be conducted at baseline and at the end of the 12-week intervention. For a comprehensive understanding of the study procedures and the timeline for the evaluation of the results, please refer to Figs. 1 and 2.

**Fig. 1 Fig1:**
[figure not shown]
Flow chart of the trial

**Fig. 2 Fig2:**
[figure not shown]
Schedule of enrolment, assessments, and interventions

### Inclusion criteria

(1) Met the diagnostic criteria for stroke, as outlined in the "Diagnostic Points for Various Major Cerebrovascular Diseases in China 2019," revised by the Expert Committee on Guideline Consensus of the Cerebrovascular Group of the Chinese Medical Association Neurology Section and the Chinese Medical Association Neurology Sect. (2) Diagnosed with mild cognitive impairment according to the criteria for "mild vascular neurocognitive disorder" as specified in the Diagnostic and Statistical Manual of Mental Disorders, 5th edition (DSM-5).(3) Experienced their first stroke with a disease duration of ≤ 1 year.(4) Aged between 45 and 75 years old.

(5) Maintained a stable condition with conscious and stable vital signs.(6) Demonstrated the ability to walk independently and safely for a distance of 10 m or more without the need for physical assistance or assistive devices.(7) Possessed the use of their dominant hand (right hand).(8) Provided informed consent and participated voluntarily in the study.

### Exclusion criteria

(1) Severe speech, visual, hearing impairments, or mental disorders that interfere with cognitive examinations.(2) Presence of other medical conditions known to cause cognitive dysfunction, such as brain tumors, traumatic brain injuries, or cerebral parasitosis, as confirmed through medical examinations.(3) Pre-existing conditions related to cognitive impairment or the use of medications targeting cognitive impairment prior to the onset of the condition, as verified by prior medical records or confirmed by a clinician or family member.(4) Beck Depression Inventory 2nd Edition (BDI-II) scores exceeding 13 points, indicating significant depressive symptoms.(5) A history of alcohol or drug abuse.(6) Concurrent serious medical conditions affecting the heart, liver, kidneys, endocrine system, or hematopoietic system.(7) Participation in other clinical trials that could influence the evaluation of this study's results.Participants meeting any of these exclusion criteria were not included in the study.

### Recruitment

This study aims to enroll stroke patients from the People's Hospital of Bao'an District, Shenzhen City, Guangdong Province, as well as its affiliated community health centers, including Dalang and Xingdong. Recruitment will be carried out by trained medical personnel who will assess eligibility based on the inclusion and exclusion criteria.Before conducting the baseline assessment, a research assistant will obtain written informed consent from individuals who express their willingness to participate in the study.

### Randomization, allocation concealment, and blinding

After the baseline assessment, eligible participants will be randomly allocated to either the Baduanjin exercise group or the routine activity control group using a randomization process. A random number grouping table will be generated based on the assigned number of cases and a random proportion. These randomization tables will be created using SAS 9.0 and managed by independent research assistants who are not involved in participant recruitment, assessment, or intervention.Independent research assistants will notify eligible participants of their assignment results via phone communication. Due to the differing forms of intervention, it is not feasible to maintain blinding for researchers, participants, and coaches throughout the experiment. However, laboratory technicians and researchers responsible for statistical analyses will remain blinded.

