### Sample size

The Montreal Cognitive Assessment (MoCA) scale served as the primary outcome measure for the final evaluation. Based on the results of a literature search, the effect size for both study groups was determined to be 0.923502 using Gpower3.1.9.2 software [21]. To achieve a test power of 0.80, a total sample size of 60 participants was calculated, with 20 participants in each group. Accounting for a potential dropout rate of 20%, the overall sample size required for this study was determined to be 72 participants, evenly distributed with 24 participants in each group.

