### Basic information

Recruiters will gather comprehensive demographic information from participants, including age, gender, ethnicity, occupation, education level, marital status, past medical history, family medical history, dietary habits, alcohol consumption, frequency of exercise, and more.In addition, prevalence data, such as the duration of stroke and the site of the lesion, as well as the presence of hemiparesis, will also be collected using a self-designed questionnaire. The degree of neurological impairment will be evaluated using the National Institutes of Health Stroke Scale (NIHSS).All baseline measurements will be conducted before participants are randomized into their respective groups.

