### Research process and data management

For the randomization process, we will utilize the Clinical Trial Public Management Platform known as ResMan, which is part of the China Clinical Trial Registry. Subjects will be assigned equally to each group at a 1:1:1 ratio.Furthermore, the research data generated during the study will be made publicly available and disseminated through this platform upon the conclusion of the study.

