### statistical analysis

The data in this study were subjected to statistical analysis using SPSS 26.0 software. All statistical tests employed a two-sided approach with a significance level (α) set at 0.05. Results were considered statistically significant when the *P*-value was ≤ 0.05 and highly significant when the *P*-value was ≤ 0.01.Count data were described using frequencies, percentages, or component ratios. Measurement data were described using mean ± standard deviation or median described.One-way ANOVA was used for data satisfying normal distribution, rank sum test for those not satisfying normal distribution, and chi-square test for count data.Multiple samples were analyzed by ANOVA, variance chi-square test for two-by-two comparisons, and LSD table for chi-square and Games-Howell table for non-chi-square.Mixed linear models were used to analyze the relationship between time and effect of interventions on cognitive function.

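### Allocation 1:1:1 to three groups of 24, two of them defined by lesion side, cannot be run as written, and holding every group at 24 would make some late assignments certain

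*Protocol article*

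**What the plan says.** Two descriptions of the allocation stand side by side in the Protocol article.

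- **Three groups.** The Abstract (Methods) names Baduanjin after left-hemisphere stroke, Baduanjin after right-hemisphere stroke, and conventional treatment, at 1:1:1. Research process and data management repeats 1:1:1. Sample size plans for "72 participants, evenly distributed with 24 participants in each group".
- **Two groups.** Study design and the Randomization section allocate to Baduanjin or control only. On the list, the latter says: "A random number grouping table will be generated based on the assigned number of cases and a random proportion". The table is made in SAS 9.0 and kept by assistants who take no part in recruitment, assessment or intervention.

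On the tool, Research process and data management says: "For the randomization process, we will utilize the Clinical Trial Public Management Platform known as ResMan". It does not say how this relates to the SAS table.

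Two further facts matter. The Randomization section accepts that "it is not feasible to maintain blinding for researchers, participants, and coaches throughout the experiment". Basic information has recruiters record items "such as the duration of stroke and the site of the lesion" before randomisation.

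**The concern.** Lesion side is a fact about the patient at entry. A patient with a left-hemisphere stroke can join Baduanjin-left or control, never Baduanjin-right. A 1:1:1 draw over the three labels therefore gives some patients a group they cannot enter, and the article has no rule for that case.

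The obvious repair, filling each group until it holds 24, has its own cost. Once a group is full, some later patients have only one possible assignment. Anyone who knows the running counts and the patient's lesion side would know that assignment before enrolling the patient. Knowledge of this kind allows patients to be delayed, declined or favoured. The resulting selection would bear on the Baduanjin versus control comparison, and the analysis could not reliably remove it.

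**Working it through.** **1. The plan's own totals.** Inputs from Sample size and statistical analysis: "the effect size for both study groups was determined to be 0.923502", power 0.80, two-sided α 0.05. Read as a standardised mean difference between two groups, a two-sample t-test needs n = 19.4, so 20 per group. Then 3 × 20 = 60, 20 × 1.2 = 24 and 3 × 24 = 72. The planned totals reproduce.

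**2. Why 1:1:1 over three labels fails.** Take a list of 24 Baduanjin-left, 24 Baduanjin-right and 24 control entries in random order, used without regard to side. Whatever the patient's side, the chance of drawing the opposite-side Baduanjin label is 24/72 = 1/3. Expected unusable assignments: 72 × 1/3 = 24. This needs no assumption about the side mix.

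**3. What a full group implies if totals are held at 24.**

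| Group that is full | Later left-sided patient | Later right-sided patient |
|---|---|---|
| Baduanjin-left | certain control | still random |
| Baduanjin-right | still random | certain control |
| Control | certain Baduanjin | certain Baduanjin |

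**4. How many assignments become certain.** This was simulated with 72 enrolments and caps of 24/24/24. An assignment counts as certain when only one open group fits the patient. The article gives neither the side mix nor a rule for reading the table, so both are assumptions.

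| Assumed scheme | Mean certain of 72, 50% left | Mean certain of 72, 40% or 60% left | Median patient at first certain assignment |
|---|---|---|---|
| One list, first entry that fits the side | about 4.5 | about 5.3 | 68 to 69 |
| Draw in proportion to open places | about 9.5 | about 11.3 | 62 to 64 |
| 2:1 draw for each patient, until capped | about 9.8 | about 12.5 to 12.8 | 58 to 62 |

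In these schemes about 2 to 10 further eligible patients find no open group for their side. Separate lists of 24 Baduanjin and 12 control for each side give a mean of 4.7 certain assignments.

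**5. Comparison: one list that ignores side.** The certain run at the end averages 1.5 assignments over three labels, or 2.4 to 2.5 for Baduanjin versus control as 48/24. With 48/24, guessing the likelier arm each time is right about 48.9 times of 72, against 48 for always guessing Baduanjin. Such a list is barely predictable.

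**6. What the proposed scheme yields.** With 2:1 within side, the expected Baduanjin group for a side is 72 × (share of that side) × 2/3.

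- 50/50 mix: 72 × 0.5 × 2/3 = 24 and 24, with 24 controls.
- 60/40 mix: 72 × 0.6 × 2/3 = 28.8 and 72 × 0.4 × 2/3 = 19.2, with 24 controls.
- For contrast, 1:1 within side at 50/50 gives 18, 18 and 36, which departs from the planned shape. The ratio therefore has to be written down.

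**The case against.** The strongest reply is that the mechanism is not in the article. The 24 per group is a planned size. No sentence says a group closes at 24, or that table entries are skipped when the side does not match. On the two-group wording alone, only about 2.4 of 72 assignments are certain, and any list of fixed length ends that way. This stands as a limit on the numbers: the 4 to 13 depends on schemes the article does not state. It does not remove the contradiction between the two descriptions, which needs no simulation.

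Three stronger readings are tempting, and the document does not support them.

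- *Once any group fills, all later assignments are certain.* This is true only when control fills. A full Baduanjin group fixes the assignment for its own side alone.
- *Staff will foresee assignments at enrolment.* Study design states allocation concealment. The list holders are separate from recruitment, and allocation follows consent and baseline. Open treatment makes knowledge of the counts possible, but nothing shows that recruiters at the hospital and its health centres have them.
- *Naming SAS and ResMan makes allocation predictable or impossible to audit.* SAS may generate the list and ResMan release it. What is unclear is which one issues the assignment.

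Block size and stratification detail may sit in the full protocol, so their absence is not counted here.

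**Conclusion.** The point holds in a limited form. It is certain from the text that the three-group and two-group descriptions conflict, and that 1:1:1 randomisation to groups partly defined by lesion side cannot be carried out. It is conditional that holding totals at 24 makes about 4 to 13 of 72 assignments certain on average. That range assumes 40 to 60% left-sided strokes and one of the reading rules above. The first certain assignment typically comes between about patient 58 and patient 69, so the exposure is confined to the end of recruitment. With one list that ignores side, it is about 1.5 to 2.5. Actual foreknowledge, and any resulting bias, is a possibility and not a demonstrated fact. The change is worth making because it resolves the contradiction and removes the forced endings at little cost.

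**What to change.** 1. Randomise Baduanjin versus control 2:1 within recorded lesion side, in randomly varying blocks whose sizes are not disclosed to site staff.
2. Do not close a group at exactly 24. Keep the overall target of 72.
3. State that ResMan issues every assignment. If a SAS table is used, it is only the hidden list uploaded to ResMan.
4. Align the Abstract, Study design, Randomization, Sample size, and Research process and data management sections to this single description.

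**Cost.** Wording and a platform set-up; no added patients. The real downside is that the two Baduanjin groups follow the side mix: 24 and 24 at 50/50, but about 29 and 19 at 60/40. At 60/40 the smaller group is below the planned 20 evaluable even before dropout, and with the planned 20% loss it leaves about 19.2 × 0.8 = 15. The Sample size section should therefore present 24 for each Baduanjin group as an expectation, not a guarantee.

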### Sample size

The Montreal Cognitive Assessment (MoCA) scale served as the primary outcome measure for the final evaluation. Based on the results of a literature search, the effect size for both study groups was determined to be 0.923502 using Gpower3.1.9.2 software [21]. To achieve a test power of 0.80, a total sample size of 60 participants was calculated, with 20 participants in each group. Accounting for a potential dropout rate of 20%, the overall sample size required for this study was determined to be 72 participants, evenly distributed with 24 participants in each group.

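### 72 randomised patients do not leave the required 60 after 20% dropout: the allowance matches 60 × 1.2, where 60 / 0.8 = 75 is needed

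*Protocol article*

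**What the plan says.** The Sample size section sizes the trial on the MoCA: "The Montreal Cognitive Assessment (MoCA) scale served as the primary outcome measure for the final evaluation". It takes the effect size from a literature search: "the effect size for both study groups was determined to be 0.923502 using Gpower3.1.9.2 software". From this it derives the number needed: "To achieve a test power of 0.80, a total sample size of 60 participants was calculated, with 20 participants in each group". The dropout step follows: "Accounting for a potential dropout rate of 20%, the overall sample size required for this study was determined to be 72 participants", which is 24 per group.

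The section gives no formula for the allowance and no other definition of the dropout rate. The Abstract and the Study design section repeat the total of 72. The section on research process and data management confirms 1:1:1 allocation. The significance level is not given with the sample size. The statistical analysis section supplies it: "All statistical tests employed a two-sided approach with a significance level (α) set at 0.05".

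**The concern.** A dropout rate is a proportion of the patients who are randomised. To end with a required number of evaluable patients, that number is divided by one minus the rate. Multiplying it by one plus the rate gives too few, because the loss then falls on the enlarged total. The step from 60 to 72 looks like the multiplication.

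If so, the required evaluable number, the dropout rate and the randomised total cannot all hold. A reader of the section would believe that the trial can lose a fifth of its patients and still have 20 per group at the stated power. There is little slack to absorb the error, because 20 per group is itself only just above the minimum that the section's effect size implies.

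**Working it through.** **Inputs**

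| Quantity | Value | Source |
|---|---|---|
| Evaluable patients required | 60 (20 per group) | Sample size |
| Dropout rate | 20% | Sample size |
| Patients randomised | 72 (24 per group) | Sample size |
| Effect size | 0.923502, metric not named | Sample size |
| Power | 0.80 | Sample size |
| Alpha | 0.05, two-sided | statistical analysis |

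**1. Reproducing the 60.** Assume that 0.923502 is Cohen's d for one comparison of two groups by a two-sided t-test at 0.05. A power of 0.80 then needs n = 19.41 per group, rounded up to 20. Three groups of 20 make 60, as stated.

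**2. Reproducing the 72.** Two rules are in use:

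- n × (1 + rate): 60 × 1.2 = 72, and 20 × 1.2 = 24 per group. This gives the stated figures exactly.
- n / (1 − rate): 60 / 0.8 = 75, and 20 / 0.8 = 25 per group. This does not.

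**3. What 72 leaves.**

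- After 20% dropout: 72 × 0.8 = 57.6 in total, and 24 × 0.8 = 19.2 per group, against the required 60 and 20.
- Largest loss that still leaves 60: (72 − 60) / 72 = 12/72 = 16.7%.
- Check on 75: 75 × 0.8 = 60, or 20 per group.

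**4. Effect on power.** Noncentral-t power for the comparison in step 1:

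| Evaluable per group | Power |
|---|---|
| 20 | 0.812 |
| 19.2 | 0.795 |
| 19 | 0.791 |

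The gap to 0.80 is 0.5 percentage points at 19.2 per group and 0.9 at 19. It stays this small because rounding 19.41 up to 20 had bought some power above the target.

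Steps 2 and 3 need no assumption about the test. Step 4 rests on the reading in step 1.

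**The case against.** The strongest reply accepts the arithmetic and disputes its weight.

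- **The effect is tiny.** With 19 patients in one group and 20 in the other, power is 0.802, so a single patient decides whether the target is met. An effect size taken from the literature is far less certain than that. This is true, and it limits how serious the point is. It does not make the figures agree.
- **The power loss depends on unstated inputs.** The section names neither the test nor the effect-size metric. Other readings of 0.923502 need fewer patients: about 16 per group for a one-sided t-test, about 49 in total for a three-group ANOVA with f = d/2, and about 15 in total with f = 0.9235. If both Baduanjin groups were pooled against control, power at 38.4 versus 19.2 would be about 0.90. This stands in part: the power figures above are conditional. But none of the three alternative sample sizes gives the article's 60, whereas the pairwise two-sided reading does. The shortfall against the stated 60 exists under any reading.
- **Dropouts are not total losses.** MoCA is also measured at week 6, and the mixed linear models can use those values from patients who miss week 12. This softens the consequence. The section, however, sizes the trial on the final evaluation and counts participants per group, so its allowance has to be right on those terms.
- **Adding 20% is a common habit, and no formula is printed.** That 60 was multiplied by 1.2 is an inference, though it gives 72 exactly. If 20% was meant only as an inflation factor, calling it a dropout rate is wrong and the sentence still needs correcting.

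**Conclusion.** The concern holds. A requirement of 60 evaluable patients, a dropout rate of 20% and 72 randomised patients are incompatible, and nothing elsewhere in the article reconciles them. The total is three patients short, one per group, or equivalently the dropout allowance is 16.7% and not 20%. This part rests only on figures printed in the Sample size section and on taking the dropout rate as a share of those randomised.

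Under the pairwise two-sided t-test reading, expected power at the stated dropout rate is 0.79 to 0.80 (0.791 with 19 per group, 0.795 with 19.2), just under the 0.80 target. The error is certain and its consequence is small. It should be corrected because the section promises a power that its own dropout rate does not deliver. It does not call the trial into question.

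**What to change.** Keep 72 and correct the sentence in one of two ways:

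- State that 72 randomised patients allow for a dropout of 16.7% while leaving 60 evaluable; or
- State that with 20% dropout about 57 evaluable patients remain, 19 per group, with power of about 0.79. In that case name the calculation behind the figure (two-sample t-test, Cohen's d of 0.923502, two-sided alpha of 0.05), provided that this is what was run.

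If the sponsor prefers to hold the 60 evaluable patients, the 20% and the 0.80 together, the randomised total becomes 75, or 25 per group. The total would then also change in the Abstract and the Study design section.

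Either of the first two options costs one sentence and makes the stated figure slightly less favourable, with no change to design, recruitment or analysis. The third costs three more patients.
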